#### Interim analysis

A single interim analysis will be performed at two years after completion of enrolment. The study is event-driven and in the interim analysis data will be analyzed to assess the appropriateness of the study hypotheses for sample size calculations. Should the expected event rates and the expected risk reduction in the outcome with the experimental intervention be higher or lower than was assumed, the duration of follow-up will be modified accordingly. The Data Safety Monitoring Committee will inform Steering Committee members if they believe that there is "no further doubt" of an existing net difference between the experimental and control intervention with regards to efficacy for the primary endpoint or if there is any novel evidence indicating that the management of patients enrolled in the study should change. An existing net efficacy difference implies at least 3 standard deviations excess or deficit in the interim analysis for the risk of the primary end-point, which could justify interruption of the study or modification of the study protocol. The Steering Committee will therefore decide if the study needs to be modified or further data are necessary.

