**Figure 1 F1:**
[figure not shown]
**Flow chart describing the selection, randomization and follow-up process of the Clinical Evaluation of the Dose of Erythropoietins (C.E. DOSE) trial**.

As there are no previous studies relating to the benefits/harms of different ESA doses for the anemia of ESKD, we established two fixed experimental doses according to the following criteria, based upon available data:

1. In the antecedent Hb target trials conducted in CKD patients [4-6], patients randomized to high (12-14 g/dL) and low (9.5-11.5 g/dL) Hb targets received between 20000 to 30000 IU/week and between 0 to 10000 g/dL IU/week of EPO, respectively.

2. In the 2004 United States Renal Data System report, 50% of hemodialysis patients incident to ESRD therapy in 1998 and followed for one year, had Hb levels between 10-13 g/dL and received more than 13000 IU/week of EPO, in particular 25% received from 13.944 to 21692 IU/week and 25% more than 21.692 IU/week of EPO [11].

Based on these assumptions the two selected experimental doses will maximize study efficacy. We will also have a safety mechanism within the trial to ensure that, after allocation to treatment, Hb values do not fall outside the safety range (of 9.5 g/dL-12.5 g/dL). A hemoglobin value above or below this range will trigger a change in the ESA dose. The prescribed ESA dose will be gradually increased or decreased by 25% until Hb values return to between 9.5 and 12.5 g/dL.

We expect recruitment to last 12 months and follow-up will be completed after 1194 cardiovascular events have occurred, which is expected to be approximately 4 years after the last patient is enrolled.

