### Statistical methods

#### Sample size

The sample size for the C.E.DOSE trial is estimated based on the following assumptions:

a) Annual incidence of the primary composite end-point of 15%, based upon data from existing trials [5,16];

b) Expected relative risk reduction in the primary composite end-point with the experimental intervention (low ESA dose) of 15% (hazard ratio = 0.85) based upon evidence from randomized trials showing increased risk of death and adverse vascular outcomes in higher Hb levels of approximately 15% [7];

c) 80% power using an alpha of 0.05;

d) A dropout rate of 5%.

Given these assumptions, 2204 individuals will be recruited. If fewer patients are randomized or the event rate of the primary endpoint is lower than expected, the duration of follow-up will be extended.

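### The interim rule lets the observed risk reduction change follow-up, which implies moving the 1194-event target; with an unadjusted final log-rank test, type I error would exceed 0.05

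*Protocol article*

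**What the plan says.** Three parts of the protocol article bear on when the trial ends.

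- **Study design:** "follow-up will be completed after 1194 cardiovascular events have occurred", expected about 4 years after the last patient is enrolled.
- **Sample size:** the design has "80% power using an alpha of 0.05" for a hazard ratio of 0.85. It adds: "If fewer patients are randomized or the event rate of the primary endpoint is lower than expected, the duration of follow-up will be extended". Both of these triggers are unrelated to the treatment effect.
- **Interim analysis:** one look, two years after enrolment closes, is used to reassess the sample-size assumptions. The text reads "Should the expected event rates and the expected risk reduction in the outcome with the experimental intervention be higher or lower than was assumed", and then "the duration of follow-up will be modified accordingly". The change is mandatory and may go either way. No formula, minimum or cap is given. The same section calls the study event-driven and sets a separate 3-standard-deviation criterion for an efficacy difference.

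The Data analysis section names a log-rank test for the comparison of the two arms. No stage weights, combination test or altered critical value is stated.

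**The concern.** An event-driven trial can change its calendar length without harm when events come slowly, because the final test still uses the planned number of events. The risk reduction is a different kind of trigger. It can be compared with the assumed 15% only by looking at interim data by arm, and acting on it means choosing the final amount of information from the interim effect. An ordinary test on the pooled data no longer has its nominal error rate under such a rule. If the early difference is large, follow-up stops while the difference is large. If it is small, the trial runs on for another chance.

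The false-positive rate of the primary comparison is at stake. The estimate that would drive the change is also weak. With about 650 events the standard error of the log hazard ratio is 2/√650 = 0.078. If the true ratio is 0.85, the interim estimate has a 95% range of about 0.73 to 0.99.

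**Working it through.** **1. The plan's own event count.** Inputs from Sample size: hazard ratio 0.85, 80% power, alpha 0.05. The sides are not stated. Freedman's formula is D = (z₁₋α/₂ + z₁₋β)² × [(1 + HR)/(1 − HR)]².

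(1.960 + 0.842)² = 7.849 and (1.85/0.15)² = 152.11, so D = 1193.9, or 1194. This matches exactly. The one-sided version gives 941, so alpha is taken as two-sided. The target therefore embodies the assumed 15% reduction.

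**2. What a different risk reduction would imply.** The same formula gives:

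| HR | Events |
|---|---|
| 0.80 | 636 |
| 0.82 | 803 |
| 0.85 | 1194 |
| 0.88 | 1927 |
| 0.90 | 2834 |

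The last figure exceeds the 2204 patients to be recruited, so any real rule would need a cap.

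**3. Where the interim falls.** Assumptions: exponential event times, uniform 12-month accrual, 5% dropout as a total loss (2204 × 0.95 = 2093.8), and 15% applied to the high-dose arm. With hazard λ, the proportion with an event two years after enrolment closes is 1 − e^(−2λ)(1 − e^(−λ))/λ.

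- 15% as a hazard: λ = 0.15 and 0.1275 give 0.312 and 0.272, mean 0.2923. 2093.8 × 0.2923 = 612 events, 51% of 1194.
- 15% as a yearly risk: λ = 0.1625 and 0.1381 give 0.333 and 0.291, mean 0.3123. 2093.8 × 0.3123 = 654 events, 55% of 1194.

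**4. Type I error with an unadjusted final test.** Let z₁ be the interim statistic at d₁ events and z₂ an independent standard normal. If the final count is D, then Z = √(d₁/D) z₁ + √(1 − d₁/D) z₂, and the null is rejected when |Z| > 1.96. Under the null, D is reset by the formula in step 1 at the observed hazard ratio (size of the log ratio, either direction) and then limited to the range from d₁ up to a cap. For extension only, D is not allowed below 1194. The worst case picks, for each z₁, the D up to the cap that makes rejection most likely.

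| Interim events | Cap | Reset both ways | Extension only | Worst case |
|---|---|---|---|---|
| 612 | 1194 | 5.8% | 5.0% | 8.6% |
| 612 | 1350 | 6.0% | 5.2% | 8.9% |
| 612 | 1800 | 6.4% | 5.6% | 9.4% |
| 654 | 1194 | 5.7% | 5.0% | 8.4% |
| 654 | 1350 | 5.9% | 5.2% | 8.7% |
| 654 | 1800 | 6.3% | 5.6% | 9.3% |

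With the cap at 1194, only shortening is possible in the reset column, so shortening alone costs about 0.7-0.8 of a percentage point.

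**5. Is the 3-standard-deviation look the cause?** No. With the target held at 1194, stopping at |z₁| ≥ 3 and otherwise testing at 1.96 gives 0.0508 (612 events) or 0.0507 (654 events). The duration clause accounts for nearly all of the inflation.

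**The case against.** **The section speaks of duration, not of 1194.** This is true, and the move of the event target is an inference. If 1194 is held and only calendar time changes, alpha is essentially kept. But the risk-reduction trigger then has no effect, since 1194 events would end the trial whatever the interim hazard ratio. The event-rate part of the sentence is harmless.

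**An unseen analysis plan may adjust the final test.** This also stands. A reader might infer that the 0.05 level is certainly lost. The document does not show that. It shows an effect-driven change beside a log-rank test with no adjustment stated, so the inflation is conditional on the test being unadjusted.

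**The size is uncertain.** It is, because no rule is given. The higher caps are also remote. Under the step 3 assumptions, about 1450-1510 events would have occurred 8 years after enrolment closes, and about 1810-1850 after 14 years. Near the planned target the inflation is at the lower end. A reader might also quote a theoretical ceiling for unrestricted changes, but that needs unlimited further events, and 2204 patients can supply at most 2204 first events. Figures from conditional-power rules would rest on a rule the protocol does not state.

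**Effect-based re-estimation can be legitimate.** Extension confined to promising interim results need not inflate alpha. This text is not so confined: it also covers shortening on a large effect and extension on a small one.

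**A changed end date reveals the interim effect.** A reader might infer this, but the document does not establish it. Effect information goes through the Data Safety Monitoring Committee, and duration may also change because of the event rate, so a new date alone would not disclose the effect.

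**Conclusion.** The point holds in conditional form. The protocol fixes a mandatory, two-way change of follow-up that depends on the observed risk reduction. In a trial that ends at the event count for HR 0.85, this amounts to moving the target on unblinded data. If the final log-rank test is not adjusted, the two-sided error is about 5.7%-6.4% for the closest mechanical reading (reset to 80% power at the observed ratio), 5.2%-5.6% for extension only with caps of 1350-1800, and about 8%-9% in the worst case of free choice. The excess under a mechanical rule is modest, but it falls on the primary test and is easily avoided.

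These figures rest on a two-sided alpha, the accrual, event-rate and dropout readings in step 3, and the assumed caps.

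**What to change.** In the Interim analysis section:

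- Remove the risk reduction as a reason to change follow-up.
- State that the target stays at 1194 first primary events whatever the interim effect.
- Let calendar follow-up change only on the pooled, blinded event rate, in line with the Sample size section.
- Keep the 3-standard-deviation rule as the only action based on the effect.

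Type I error is then about 0.050-0.051.

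If an effect-based change is wanted, prespecify the rule, with its minimum and cap, and a final test that combines the two stages with weights fixed in advance: √t z₁ + √(1 − t) z₂, with t the planned information fraction. This held 0.050 under the effect-driven changes simulated. With the 3-standard-deviation look included, a final critical value of about 1.966 keeps it there for t of 0.51-0.55.

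The cost is one or two sentences of amendment. The sponsor gives up the ad hoc option to shorten or extend on the observed effect.

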## Discussion

On the basis of current evidence, the optimal therapeutic strategy for the management of anemia of ESKD is still unclear. In light of evidence of increased harm and limited benefit from targeting Hb levels, Hb target trials are no longer necessary. The C.E.DOSE study is the first study to test a new therapeutic approach for the management of anemia of ESKD, based on fixed ESA dose. We will compare the effects of two fixed ESA doses, a maximum vs a minimum dose, in order to shed light on the optimal intervention for anemia of hemodialysis patients improving cardiovascular events, quality of life and costs.

## List of abbreviations

CERA: continuous erythropoietin receptor activator; CKD: chronic kidney disease; DARBO: darbopoetin; EPO: erythropoietin; ESA: erythropoietin stimulating agents; ESKD: end stage kidney disease; Hb: haemoglobin; PROBE: prospective randomized open blinded end-point; QoL: quality of life.
